# Effects of oral *Nigella sativa* oil on the expression levels and serum concentrations of adiponectin, PPAR-γ, and TNF-α in overweight and obese women: a study protocol for a crossover-designed, double-blind, placebo-controlled randomized clinical trial

**DOI:** 10.1186/s13063-019-3568-0

**Published:** 2019-08-17

**Keywords:** Obesity, Overweight, *Nigella sativa*, Tumor necrosis factor-alpha, Adiponectin, Peroxisome proliferator-activated receptors

## Abstract

**Background:**

Obesity is a major public health problem in recent decades. The accumulation of excessive fat promotes inflammatory status. Meanwhile, herbal products are marketed for their weight-loss properties, such as *Nigella sativa* (*N. Sativa*) which has been used for centuries to treat rheumatoid arthritis, diabetes, and asthma; recently, the anti-obesity characteristics of *N. sativa* have also been indicated. However, the exact mechanisms and cellular-related pathways are still unclear. Thus, we will aim to assess the effects of oral *N. sativa* on the gene expression of inflammatory and adipogenesis-related factors, including TNF-α, PPAR-γ, and adiponectin as well as assessing their serum concentrations among obese and overweight individuals.

**Methods:**

Obese and overweight women aged 25–55 years with a body mass index (BMI) of 25–35 kg/m^2^ will be recruited from the Obesity Clinic in Shahid Sadoughi University of Medical Sciences and will be assessed for eligibility against inclusion criteria. They will be randomly assigned into two groups to receive either two capsules of *N. sativa* or two capsules of placebo per day for eight weeks (each capsule contains 1000 mg of *N. sativa* or placebo). There will be a four-week wash-out period and then participants will receive the reverse supplements for another eight weeks. Biochemical assessments and gene expressions (using real-time polymerase chain reaction) will be conducted at the beginning and at the end of every intervention period.

**Discussion:**

The present study will investigate the probable cellular pathways for the anti-obesity effects of *N. sativa* in overweight/obese women.

**Trial registration:**

Iranian Registry of Clinical Trials, IRCT20180528039884N1. Registered on 2nd of July, 2018.

**Electronic supplementary material:**

The online version of this article (10.1186/s13063-019-3568-0) contains supplementary material, which is available to authorized users.

## Background

The epidemic of overweight and obesity presents a major challenge to health around the world. Obesity is defined as the accumulation of abnormal or excessive fat that may interfere with the maintenance of an optimal state of health [1]. The excess of macronutrients in the adipose tissues stimulates them to release inflammatory mediators such as tumor necrosis factor alpha (TNF-α) and reduces production of adiponectin, predisposing to a pro-inflammatory state and oxidative stress [2].

Among the adipokines, adiponectin is widely recognized for its anti-diabetic, anti-inflammatory, anti-atherogenic, and cardio-protective effects and shows protective activity in various processes such as energy metabolism and inflammation [3]. In humans, plasma levels of adiponectin are decreased in cases of insulin resistance and obesity [4]. One of the molecular mechanisms of adiponectin may be direct actions via downregulating of inflammatory responses involving TNF-α [5]. In obesity, alterations in the gene expression of adiponectin and its receptors reduce adiponectin sensitivity leading to insulin resistance [3].

On the other hand, peroxisome proliferator-activated receptors (PPARs) are a group of nuclear receptors with various isoforms, including α, β/δ, and γ, that are involved in transcription regulation of a broad range of genes related to inflammation and energy homeostasis and represent important targets for obesity, obesity-induced inflammation, and metabolic syndrome. PPAR-γ is a transcription factor abundant in adipose tissue which has been known to regulate adipocyte differentiation and fatty acid storage [6]. More recently, PPAR-γ has been recognized as playing an important role in inhibiting the expression of inflammatory cytokine [7]. Obesity has been reported to induce a decline in the activity and amount of PPAR-γ. This correlation appears to be strongly associated with the pathogenesis of obesity [8]. An association between adiponectin and PPAR-γ has been reported by Yadav et al.; they revealed that adiponectin can mediate phosphorylation of adenosine monophosphate-activated protein kinase and also PPARs, after binding to its receptors and thereby increase fatty acid oxidation [9]. An animal study on rats reported that increased adiponectin levels and improvements in insulin sensitivity after a weight-reduction intervention, might be due to an increase in PPAR-γ levels [10].

With regard to the relation between TNF-α and obesity, plasma concentration of TNF-α and its receptors were found to be higher in obese individuals, which may get alleviated with weight loss [11]. Interestingly, TNF-α is reported to have a correlation with PPAR-γ activity. Studies revealed that TNF-α might have inhibitory effects on PPAR-γ which is involved in the pathogenesis of inflammation [12, 13]. Furthermore, a previous study reported that PPAR-γ activity could be regulated by TNF-α at pre-translational and post-translational levels [13]. More recently, the long-term assessment of anti-TNF-α inhibitor treatment to individuals diagnosed with metabolic syndrome has been shown to increase adiponectin levels, confirming a role for TNF-α in obesity-related insulin resistance in humans [12]. Moreover, TNF-α inhibits the conversion of pre-adipocytes to mature adipocytes, notably through downregulating adipogenic genes such as PPAR-γ, allowing further recruitment of uncommitted cells and, thus, possible expansion of adipose tissue mass [14]. TNF-α also downregulates the messenger RNA (mRNA) levels of adiponectin [15] while, conversely, adiponectin suppresses lipopolysaccharide-induced TNF-α production [5].

Studies have shown that losing weight in obese individuals can result in an increase in adiponectin levels and the expression of its receptors [3, 15]. Meanwhile, herbal products are widely marketed for their weight-loss properties [16]. *Nigella sativa* (*N. sativa*) is a traditional herbal medicine that has been used for centuries to treat rheumatoid arthritis, diabetes, asthma, and other metabolic disorders. Recently, anti-obesity characteristics of *N. sativa* have also been indicated [17]. The exact mechanism of anti-obesity effects of *N. sativa* is unclear; bioactive components of *N. sativa* including Thymoquinone, inhibitory components of lipase, unsaturated fatty acids, and its appetite-reducing effect are involved in probable mechanisms for anti-obesity effects of *N. sativa* [18]. Additionally, *N. sativa* has suggested to act as an agonist of PPAR-γ which impacts upon energy homeostasis, thus enhancing the expression of lipogenic genes [19]. Concerning the effects of *N. sativa* on gene expression, there are only in vitro, in vivo, and/or animal trials that evaluated the effects *N. sativa* or its major active component, Thymoquinone, on the gene expression of various factors such as TNF-α, adiponectin, or PPAR-γ, and reported beneficial improvements in inflammation [20–27]. Nevertheless, the probable mechanisms of *N. sativa* involving the gene expressions of factors related to obesity and its pathogenesis have not yet been investigated in human studies.

Few clinical trials assessed the effects of *N. sativa* on serum concentrations of inflammatory markers and adipokines [18, 28–30]. Mahdavi et al. investigated the effects of *N. sativa* oil supplementation combined with a low-calorie diet on TNF-α [30] using a parallel-randomized design and reported that *N. sativa* oil may help to better manage weight and inflammatory status in obese women [28].

To the best of our knowledge, there are no clinical trials that assessed the effects of *N. sativa* or Thymoquinone through the TNF-α, PPAR-γ, or adiponectin pathways in obesity.

Consequently, the present clinical trial aimed to investigate the following objectives:
To assess the effects of oral *N. sativa* oil on the gene expression of TNF-α, PPAR-γ, and adiponectin along with the changes in serum concentrations of these factors among obese and overweight women.To conduct a crossover, placebo-controlled, randomized clinical trial (RCT), to compare the altered gene expression as well as other outcome measures of every individual with herself, as her own control, and with the control group to achieve more accurate results.To investigate the alterations in serum levels of liver enzymes including alanine transaminase (ALT), aspartate transaminase (AST), and alkaline phosphatase (ALP) as well as measuring lipid profile including total cholesterol, triglyceride, high density of lipoprotein cholesterol (HDL-C), low density of lipoprotein cholesterol (LDL-C), and atherogenic indices before and after every intervention period.

## Materials and methods

### Study design

The design of the present study is a crossover, double-blind, placebo-controlled RCT which will be conducted among obese and overweight women for 20 weeks. Participants will receive either a daily dose of *N. sativa* or placebo for eight weeks in two phases separated by a wash-out period of four weeks. Each participant will be reversed for the second phase of the intervention according to the randomized crossover design. This study will be conducted in the Obesity Clinic of Shahid Sadoughi University of Medical Sciences, Yazd, Iran. The overview of the study is presented in Fig. 1. Moreover, this article will be reported according to the Standard Protocol Items: Recommendations for Interventional Trials (SPIRIT) statement [31]. A SPIRIT diagram detailing the timing of enrolment, interventions and assessments is provided in Fig. 2. A completed SPIRIT checklist is also provided in Additional file 1. Any methodological changes in the study design or sample size, which may potentially affect the participants’ safety or study procedures, will be discussed in the committee of ethics before the study initiation.

**Fig. 1 Fig1:**
[figure not shown]
The overview of the study

### Eligibility of criteria

Obese and overweight women aged 25–55 years with a body mass index (BMI) of 25–35 kg/m^2^ will be recruited from the Obesity Clinic in Shahid Sadoughi University of Medical Sciences. Exclusion criteria will include: cardiovascular diseases; hepatic, pancreatic, thyroid, or renal problems; having allergies to *N. sativa*; or a history of having a weight-reduction diet or program in the six months before the study. Furthermore, taking any anti-obesity medications or any herbal and anticoagulant agents including aspirin, vitamin E, vitamin K, and warfarin in the six months before the study as well as being either pregnant, lactating, or having uncontrolled polycystic ovary syndrome will also be considered exclusion criteria.

### Randomization and blinding

The present crossover, double-blind, placebo-controlled RCT will be consisted of two intervention periods of eight weeks each. Participants will be randomized 1:1 using stratified block randomization based on age (25–40 years and 40–55 years). One of the main researchers will use computer-generated random numbers to randomly allocate eligible participants into the intervention or control groups using sealed envelopes. Participants and administrators will be blinded to the content of the bottles, study treatment, and allocation until the final analysis. Individuals will be asked about their treatment group at the end of each intervention period. Their prediction will then be compared with the true assignments. Participants will receive four bottles for the entire 20-week intervention. Each bottle will contain 56 capsules and every participant will receive two bottles during every intervention period (one bottle at the beginning of week 1 and one bottle at the end of week 4 of every intervention duration).

Participants will be also asked about any possible reactions or different feeling after receiving the treatments at the end of every intervention period. No forms will be recorded, since the treatment doses were regarded as safe in the previous investigations.

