### Compliance

Compliance with consumption will be monitored every other day through phone interviews which will be followed by face-to-face interviews once a week. Participants will be asked to consume one capsule before lunch and one capsule before dinner; this will also increase their compliance with consumption. All participants will be requested to bring back their first bottle at the end of the primer intervention and then they will be given the second bottle of supplements. If the remaining capsules of every participant will exceed 10% of the total administered supplements (12 capsules), the participant will be categorized as non-adherent. All individuals, including those who will complete the study or those who will not complete for any reasons, will follow the same schedule.

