### Matching energy intakes between groups

With regard to the dietary energy intakes of participants, we decided to give every individual an iso-energy dietary program in order to match every participant based on their energy and macronutrient intakes. Hence, an eight-week one-to-one individualized iso-energy dietary program for every intervention period, based on every participant’s current weight, will be performed. After determination of required energy, the registered dietician will develop a plan of servings from each food group that will fulfill the macronutrient distribution. The required participants’ daily energy intake will be distributed as follows: < 30% from fat (mainly mono-unsaturated and poly-unsaturated fatty acids); 55% from carbohydrates; and 1.2–1.5 g protein per kg of body weight. After baseline measurements, each participant will meet the registered dietitian three times during each intervention period (at weeks 0, 4, and 8).

Dietary intake will be quantified using three-day food records, including one weekend day and two weekdays as well as 24-h food recalls. Daily macro- and micro-nutrient intakes will be calculated by analyzing food data using nutritionist IV software (First Databank, San Bruno, CA, USA) modified for Iranian foods.

Shahid Sadoughi University of Medical Sciences will be responsible for any related problems; adverse events will be reported to the medical ethics committee from the initiation of the study. Participants may withdraw from the study for any reason at any time.

General information including age, diseases, medications, and supplements will be recorded through interviews at the beginning of the study. Physical activity level will be calculated through a questionnaire using metabolic equivalents (METs) at the beginning and at the end of every intervention period. Results of the assessments will be shared for every participant separately.

Primary outcomes consist of gene expression and serum concentration levels of adiponectin, PPAR-γ, and TNF-α. Secondary outcome measures consist of blood levels of lipid profiles and anthropometric measurements. The assessments of the outcomes are listed below.

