### Biochemical measurements

A total of 12 mL fasting blood sample of venous blood will be collected from every participant. Circulating adiponectin and TNF-α will be assessed by enzyme-linked immunosorbent assay (ELISA). Blood pressure will be measured with a well-validated automated digital blood pressure monitor (Beurer, Germany, BM 85), following American Heart Association guidelines. Biochemical analyses including total cholesterol, triglycerides, HDL-C, LDL-C as well as liver enzymes, including ALT, AST, and ALP, will be measured using automated enzymatic methods. The values of atherogenic factors, including the ratios of HDL-C/LDL-C and LDL-C/HDL-C, will be calculated. All laboratory data will be identified by an ID number to maintain the participants’ confidentiality.

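### Reactions are asked about at period end with no form kept, which conflicts with the commitment to report adverse events and leaves symptomatic reactions without a systematic record

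*Protocol article*

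**What the plan says.** Three sections of the protocol article bear on this point, and a fourth supplies related data.

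- **Randomization and blinding** schedules one question about reactions: "Participants will be also asked about any possible reactions or different feeling after receiving the treatments at the end of every intervention period". The next sentence is "No forms will be recorded, since the treatment doses were regarded as safe in the previous investigations". The same section says that the trial "will be consisted of two intervention periods of eight weeks each".
- **Matching energy intakes between groups** says that "adverse events will be reported to the medical ethics committee from the initiation of the study". It names no form, log or other instrument for collecting them.
- **Compliance** provides frequent contact with participants: "Compliance with consumption will be monitored every other day through phone interviews which will be followed by face-to-face interviews once a week". The stated purpose is capsule consumption; reactions are not mentioned.
- **Biochemical measurements** says that "liver enzymes, including ALT, AST, and ALP, will be measured using automated enzymatic methods", and also plans blood pressure. The Abstract says of the biochemical assessments and gene expressions that they "will be conducted at the beginning and at the end of every intervention period".

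The primary and secondary outcomes listed under Matching energy intakes between groups include no adverse-event outcome.

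**The concern.** A condensed article may well leave out its adverse-event form, and that alone would be no finding. Here the article states a decision not to keep one and gives a reason. The reason concerns safety, so the decision is about safety recording. Earlier opinion that a dose is safe does not justify leaving reactions unrecorded in a blinded, placebo-controlled trial, which is the setting best able to test that opinion.

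Two things are at stake. The first is the commitment to the ethics committee: reliable reporting from the first day needs a record kept from the first day. The second is information that the crossover gives almost free. Each woman who completes both periods can supply a pair of observations, her reactions on N. sativa and her reactions on placebo. Without dated entries tied to a period and a treatment code, that pair cannot be reconstructed reliably, and a withdrawal cannot be linked to a symptom. A later statement that the product was well tolerated would lack systematic data on symptoms. In addition, the one stated time for asking comes after eight weeks, when minor or early reactions may have been forgotten.

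**Working it through.** No arithmetic decides this point and the plan states no figure to reproduce. The check sets the sections side by side.

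1. **When are reactions asked about?** At the end of each intervention period (Randomization and blinding). With two periods, that is two scheduled questions per woman, each covering eight weeks. The text states no other time for asking. The schedule figure (Fig. 2) was not available for this check.

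2. **Where do the answers go?** On no form, by explicit statement in the same section. No alternative place for them is described.

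3. **What is owed to the ethics committee?** Reports of adverse events from the start of the trial (Matching energy intakes between groups). That duty runs throughout, whereas the only scheduled question comes at period end.

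4. **Can the statements in 2 and 3 both be followed?** In part. An event that someone notices and forwards would leave a trace in the report itself. A reaction elicited at period end, or mentioned in a phone call, has no stated place to be written down. Whether it reaches the committee then depends on individual memory and judgement. Reporting is possible but not reliable.

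5. **What safety-related data will exist?**

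| Source | Planned? | Can it be compared between treatments? |
|---|---|---|
| ALT, AST, ALP | Yes, start and end of each period | Yes |
| Blood pressure | Yes; no separate timing is given | Yes, if taken in each period |
| Reports to the ethics committee | Yes | Incomplete, with no systematic collection behind them |
| Symptomatic reactions by date, period and code | No form, by stated choice | No |

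The gap is the last row. Laboratory values and blood pressure do not capture symptoms, so the other rows cannot fill it.

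6. **Would closing the gap need new contacts?** No. Alternate-day calls over 8 weeks (56 days) give 56 / 2 = 28 calls per period. For 40 women and two periods this is 28 × 2 × 40 = 2,240 calls. Weekly interviews add 8 × 2 × 40 = 640. These contacts are already planned for compliance, and a form would be filled in only when a reaction is reported.

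**The case against.** The strongest reply is that the sentence rules out forms, not all recording. It stands in the blinding section, directly after the check of participants' treatment guesses, and speaks of reactions or different feelings. It could mean only that minor sensations get no standard form, while adverse events proper are governed by the later commitment. This reading is possible, and it is why the two statements cannot be called strictly impossible to follow together. It does not remove the fault. The article draws no line between a reaction and an adverse event, and it justifies the absence of forms by safety.

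Three stronger readings are tempting, and the document does not support them.

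- *A reader might infer that the trial will have no safety data at all.* Liver enzymes before and after each period and blood pressure are planned, and reports to the committee would leave some record.
- *A reader might infer that reactions can come to light only after eight weeks.* The article states no other time for asking, but women are to be "monitored every other day through phone interviews which will be followed by face-to-face interviews once a week", and they may mention a troublesome symptom at any of these contacts.
- *A reader might infer from the exclusions that the plan itself recognises hazards of the product and then declines to record them.* Apart from allergy to N. sativa, which is product-related on its face, the eligibility section gives no reasons. Avoiding confounding of the inflammatory outcomes would explain much of the list equally well.

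It is also fair to say that safety is neither a stated objective nor an outcome, and that the primary comparison is unaffected. This limits the consequence to safety reporting. It does not settle the conflict with the commitment to the ethics committee.

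**Conclusion.** The point holds in a limited form. The article states a rule which, if followed, leaves symptomatic reactions without a systematic record by period or treatment, and this conflicts with its own commitment to report adverse events from the start. Such reactions could then not be reliably reported, attributed to a period or compared between N. sativa and placebo.

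The size cannot be expressed as a number. The gap covers symptomatic reactions in both periods for all women; it does not cover liver enzymes or blood pressure, and it does not bias the primary outcomes. The conclusion assumes that no forms means no systematic written record of the elicited reactions, and that no other document supplies one. If a full protocol does contain an adverse-event log, the sentence in the article is wrong and still needs correcting.

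**What to change.** Reconcile the two sections as follows.

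- Delete the sentence that no forms will be recorded, together with its justification.
- Record each reported reaction on a short form: date, description, severity, period and blinded bottle code (A or B). Use it at the period-end question and at the phone and weekly contacts already planned.
- Report adverse events to the ethics committee as the article already says, with these forms as the source.
- Tabulate reactions by treatment received, with withdrawals due to reactions shown separately.

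The section on Trial status says that initial recruitment is complete, so some exposure may already have passed. For any exposure completed without recording, the trial report should state that reactions were not systematically recorded and should make no tolerability claim from them.

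The cost is one short form and a small amount of extra data entry. Grading severity needs some qualified judgement. No new visits are required.
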